### Hypotheses

Spray-on autologous skin grafting improves wound healing time in patients with DFU compared with standard careSpray-on autologous skin grafting is cost-effective when compared with standard care

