### Secondary outcomes

Secondary outcomes include: i) index ulcer free days at 12 months, ii) time to full epithelialisation of the index ulcer, iii) trajectory of wound healing of the index ulcer (defined as volume and measured using Silhouette™), iv) major adverse events, v) any minor or major lower limb amputation, vi) all-cause mortality, vii) re-ulceration of the index ulcer, viii) the development of any new ulcers ix) total costs of inpatient and outpatient costs (see economic analysis, below), x) readmission to hospital and xi) health-related quality of life (as measured by EQ-5D-5 L) [22].

The definitions for secondary outcomes are consistent with international guidelines [23]. Re-ulceration is defined as healing of index ulcer followed by subsequent ulceration with loss of epithelialisation at the same location. A minor amputation is an amputation below the ankle including toe, metatarsal-phalangeal and midfoot amputations. A major amputation is an amputation above the ankle including below knee and above knee amputations. New onset infection includes infections that have commenced during the preceding 2 weeks, including existing ulcers that have never previously been infected.

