## Statistical considerations

### Primary and secondary outcomes

All analyses will be conducted according to the intention-to-treat principle. Baseline characteristics will be compared by treatment group. Effects of treatment on the primary study endpoint (complete healing of the index ulcer at 6 months) will be estimated with the use of unadjusted logistic regression with last observation carried forward for those lost to follow-up. All *P*-values will be two-sided and *P*-values less than 0.05 will be considered to indicate statistical significance. Multiple logistic regression will be applied to adjust for prognostic factors such as vascular insufficiency and site of DFU (fore-, mid- or hind foot) which are strongly correlated with the outcome (*r* ≥ 0.3) [25, 26]. Binary secondary outcomes at 12 months will be analysed similarly. For continuous secondary outcomes, change score analysis that determines treatment effect based on the difference between baseline and post treatment score (basic adjustment) will be undertaken. Multiple linear regression adjusting for i) the baseline value of the outcome variable in the model (model 1), and ii) model 1 + adjustment for prognostic baseline factors (model 2) will be undertaken. Data will be analysed using IBM SPSS Statistics 25.

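### Neither stated rule for secondary outcomes fits time to full epithelialisation, the direct test of the healing-time hypothesis; re-ulceration in all randomised patients also needs care in interpretation

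*Protocol article*

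**What the plan says.** The first hypothesis in the protocol article (Hypotheses) is that spray-on skin "improves wound healing time in patients with DFU". The section Secondary outcomes opens its list with "i) index ulcer free days at 12 months, ii) time to full epithelialisation of the index ulcer" and defines one later item thus: "Re-ulceration is defined as healing of index ulcer followed by subsequent ulceration with loss of epithelialisation at the same location".

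Under Statistical considerations (Primary and secondary outcomes), every analysis is to follow intention to treat. Two rules are then given for secondary outcomes:

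- **Binary:** "Binary secondary outcomes at 12 months will be analysed similarly", that is, by logistic regression as for the primary outcome.
- **Continuous:** "For continuous secondary outcomes, change score analysis that determines treatment effect based on the difference between baseline and post treatment score", and then "Multiple linear regression adjusting for i) the baseline value of the outcome variable in the model (model 1"), with a second model that adds prognostic factors to the first.

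No method for censored data is named anywhere in the article. Costs are listed as "total costs of inpatient and outpatient costs (see economic analysis, below") and have their own bootstrap cost-effectiveness method under Health economic analyses.

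**The concern.** Time to healing is not observed for a patient who has not healed. It also has no value at randomisation from which to take a change or for which to adjust. The change score and the first regression model are therefore undefined for it, and the second model is built on the first.

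If an analyst sets the baseline term aside and fits a linear regression anyway, there are two options. One keeps only healed patients, a subset formed after randomisation and affected by treatment, which conflicts with intention to treat. The other assigns unhealed patients a time, and the article gives no rule for that time. In an open-label trial, this choice should not be left until the data are seen.

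Re-ulceration has a related problem. A patient who never heals cannot re-ulcerate, so a logistic comparison in all randomised patients counts treatment failures as free of the event. The arm that heals more ulcers has more patients at risk and can look worse.

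**Working it through.** **Inputs from the article.** Healing at 6 months of 45% and 70%, 5% significance, 80% power, 136 patients needed and 150 recruited (Study design); two-sided tests (Primary and secondary outcomes); visits at 26 and 52 weeks (Follow up measurements).

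**Assumptions not in the article.** Equal allocation (75 per arm), no dropout, and the two healing-time models below.

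**1. The plan's own figure.** Without correction, n per arm = [1.960·√(2·0.575·0.425) + 0.8416·√(0.45·0.55 + 0.70·0.30)]² / 0.25² = (1.370 + 0.569)²/0.0625 = 60.2, or 122 patients in total. With continuity correction, n = (60.2/4)·[1 + √(1 + 4/(60.2·0.25))]² = 67.95, so 68 per arm and 136 in total. The stated 136 reproduces. It concerns the binary primary outcome and does not change.

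**2. Extent of censoring.** Unhealed at 26 weeks: 1 − 0.45 = 55% and 1 − 0.70 = 30%. With constant hazards, unhealed at 52 weeks: 0.55² = 30% and 0.30² = 9%. Censoring is heavy and unequal between arms.

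**3. Size of effect under constant hazards (model a).** Daily rates are −ln(0.55)/182 = 0.00328 and −ln(0.30)/182 = 0.00662, a hazard ratio of 2.01.

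- Restricted mean to 52 weeks, (1 − S)/λ: 0.6975/0.00328 = 212 days and 0.91/0.00662 = 138 days, using unrounded rates. The difference is 75 days.
- Mean among those healed by 52 weeks, 1/λ − 364·S/(1 − S): 304.4 − 157.9 = 146.6 days and 151.2 − 36.0 = 115.2 days. The difference is 31 days.

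The healed-only comparison thus shows less than half of the restricted-mean difference.

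**4. Power.** 4,000 simulated trials with 75 per arm. Model (b) has 45% and 70% healing, uniformly over weeks 4 to 26 in both arms, with no later healing. The linear comparison is of arm means, without covariates.

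| Analysis | (a) 52 wk | (a) 26 wk | (b) 52 wk | (b) 26 wk |
|---|---|---|---|---|
| Linear, healed only | 41% | 13% | 6% | 6% |
| Linear, unhealed set to end of follow-up | 96% | 84% | 87% | 66% |
| Log-rank, all randomised | 97% | 90% | 87% | 87% |

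Under (b) the healed-only difference is about 0 days although the hazard ratio is about 2. Under (a), setting unhealed patients to end of follow-up gives a 74-day difference at 52 weeks, close to the restricted-mean value of 75.

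**5. Re-ulceration at 12 months.** Take healing of 69.75% and 91% from step 2 and the same assumed risk r per healed ulcer in both arms:

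- r = 20%: 0.1395 v 0.182, odds ratio 1.37
- r = 30%: 0.209 v 0.273, odds ratio 1.42
- r = 40%: 0.279 v 0.364, odds ratio 1.48

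All three go against spray-on skin although the risk per healed ulcer is equal.

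**The case against.** The strongest reply is that the article never classes time to healing as a continuous outcome. A change score cannot be computed for it, so the article may simply be silent and an analysis plan not shown may supply a survival method. The first part is true and the second is possible. That is why one cannot say that the first hypothesis will be answered wrongly, though a reader might infer it. What remains is that the article states rules for secondary outcomes, makes no exception for this one, and neither rule gives a sound result for it.

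A second reply is that linear regression need not drop unhealed patients. This also stands: with unhealed patients set to end of follow-up and no dropout, power at 52 weeks is 87–96%. The low figures of 41% and 6% belong to a healed-only analysis that the article does not prescribe. The article prescribes neither version, and the result depends heavily on which is used.

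A reader might also extend the point to other outcomes. The article does not support that:

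- **Costs** are sent to the economic section, which has its own method.
- **Ulcer-free days** start at zero for everyone, so the change score equals the 12-month value and the constant covariate drops out. Only a clarification is needed.
- **Wound volume** has a baseline, and baseline-adjusted regression is valid for it. A model using all visits may be more efficient, but that is a preference.

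On re-ulceration, the 20–40% risk is assumed, and index ulcer-free days already give a net measure in all randomised patients. Odds ratios above about 1.5 arise only by using 6-month healing, whereas the stated rule is for 12 months.

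**Conclusion.** The point holds for time to full epithelialisation and, as a matter of interpretation, for re-ulceration. For the former, the stated continuous-outcome rule is undefined. If forced, it either selects on a post-randomisation event or needs a coding rule that is not given. Power at 52 weeks then runs from 6% to 96%, depending on that choice and on the healing-time model, against 87–97% for log-rank. For the latter, equal risk per healed ulcer would appear as an odds ratio of about 1.4–1.5 against the arm that heals more.

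The 55% and 30% unhealed at 26 weeks follow from the article's own rates. The 52-week proportions and all power figures rest on the assumed healing-time models, equal allocation and no dropout; the odds ratios rest on constant hazards and the assumed re-ulceration risk. The primary outcome, its logistic analysis and the sample size are unaffected. This should be fixed, but it does not threaten the main result.

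**What to change.** - **Continuous rule:** restrict the change score and baseline-adjusted regression to outcomes measured at baseline (EQ-5D-5L, wound volume).
- **Time to full epithelialisation:** analyse all randomised patients with Kaplan-Meier or cumulative incidence curves and a log-rank test or Cox model, censored at last contact, with death and index-limb amputation as competing events.
- **Ulcer-free days:** state that arms are compared directly at 12 months, with no change score.
- **Re-ulceration:** interpret the all-randomised comparison beside the proportion healed and still healed at 12 months in all randomised patients, and report re-ulceration among healed patients descriptively.

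The cost is a few sentences and a little programming, with no new data, because healing, amputation, death and re-ulceration are already collected. The change should be made before any comparison by arm is seen. If an analysis plan already contains these methods, aligning the published text with it is enough.

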## Study design

This study is a prospective, randomised, open label trial powered for superiority. Local and international data informed sample size calculations indicating that, at present, 45% of patients with DFU will achieve complete healing at 6 months [17, 18, 21]. We estimate that 136 (with continuity correction) patients are required to have 80% chance of detecting, at the 5% level of significance, an increase in the primary outcome measure from 45% in the control group to 70% in the spray-on skin group [19]. To account for drop-outs, we will aim to recruit 150 participants in total.

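### Continuous secondary outcomes get three analyses, all read at P<0.05, and the more efficient baseline-adjusted model is not made the lead

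*Protocol article*

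**What the plan says.** The relevant text is in the protocol article, Statistical considerations, under Primary and secondary outcomes. For continuous secondary outcomes it plans:

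- a change score: "change score analysis that determines treatment effect based on the difference between baseline and post treatment score (basic adjustment) will be undertaken";
- model 1: "Multiple linear regression adjusting for i) the baseline value of the outcome variable in the model (model 1";
- model 2: "ii) model 1 + adjustment for prognostic baseline factors (model 2) will be undertaken".

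The same paragraph sets one significance rule: "All *P*-values will be two-sided and *P*-values less than 0.05 will be considered to indicate statistical significance". It states no order of priority among the three analyses and no follow-up time point for them.

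The Secondary outcomes section lists wound volume trajectory, EQ-5D-5L, index ulcer-free days and costs, among others. Under Follow up measurements, EQ-5D-5L is taken at baseline, 26 and 52 weeks. Wound volume is measured at 4, 10, 18, 26, 39 and 52 weeks. The article does not mention a baseline volume there, but a change score presupposes one.

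**The concern.** A change score fixes the slope of follow-up on baseline at 1. Model 1 estimates that slope from the same data. In a randomised trial both are unbiased, but unless the true slope is 1 the change score over- or under-corrects chance baseline differences and has the larger variance. The plan therefore contains an efficient analysis without giving it priority.

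What is at stake depends on how the paragraph is read:

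- **The change score leads.** Results for EQ-5D-5L and wound volume then rest on the less precise estimate.
- **Nothing leads.** Three correlated P-values exist per outcome, each eligible to be called significant, and the choice among them can be made after the results are seen. The trial is open label.

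The paragraph is also written for continuous secondary outcomes in general. Ulcer-free days and costs accrue after randomisation, so neither a change score nor model 1 can be formed for them.

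**Working it through.** **Reference sample size.** The plan gives no figure for the continuous outcomes, so I took the analysed number from Study design: 136 patients, 80% power, two-sided 5%, with healing moving "from 45% in the control group to 70% in the spray-on skin group". With the pooled-variance formula, mean proportion 0.575 and difference 0.25:

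- n = [1.96·√(2·0.575·0.425) + 0.8416·√(0.45·0.55 + 0.70·0.30)]² / 0.25² = 60.2, rounded up to 61 per arm (122 in total).
- With continuity correction: (60.2/4)·[1 + √(1 + 4/(60.2·0.25))]² = 67.9, rounded up to 68 per arm, or 136.

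The stated 136 is reproduced. The target of 150 allows for 14/150 = 9.3% drop-out. I use 68 per arm below. Equal allocation is assumed: the block sizes of 2, 4 and 8 fit it, but no ratio is stated.

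**Reading A: the change score leads.** Let r be the baseline to follow-up correlation and s the common SD. Neither is in the document; r is varied.

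- Change score: residual variance 2s²(1−r).
- Model 1: residual variance s²(1−r²).
- Ratio: 2(1−r)/(1−r²) = 2/(1+r).

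Take an effect for which model 1 has 80% power. The change-score power is then Φ[(1.96 + 0.8416)·√((1+r)/2) − 1.96], and 136 patients are worth 136·(1+r)/2.

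| r (assumed) | Variance ratio | Change-score power (model 1 = 80%) | Equivalent number of 136 |
|---|---|---|---|
| 0.3 | 1.54 | 62% | 88 |
| 0.5 | 1.33 | 68% | 102 |
| 0.7 | 1.18 | 73% | 116 |
| 0.9 | 1.05 | 78% | 129 |

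Equal SDs are doubtful for wound volume, because healed ulcers have volume zero. If the follow-up SD is k times the baseline SD, the ratio becomes (k² + 1 − 2rk)/[k²(1−r²)] = 1 + (1−rk)²/[k²(1−r²)]. This is never below 1, and it equals 1 only when rk = 1. At k = 0.75 it is 2.17 for r = 0.3 and 1.79 for r = 0.7. At k = 0.5 it is about 4. These k values are assumptions and show direction only.

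**Reading B: nothing leads.** The three analyses were simulated with no treatment effect: 20,000 trials per setting, 68 per arm and two prognostic covariates. The covariates' combined correlation g with the part of the outcome not explained by baseline was 0.3 or 0.5. Each model alone rejected in 4.8% to 5.4% of trials. At least one of the three rejected as follows:

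| r (assumed) | g = 0.3 | g = 0.5 |
|---|---|---|
| 0 | 10.2% | 10.1% |
| 0.3 | 9.2% | 9.9% |
| 0.5 | 8.7% | 9.2% |
| 0.7 | 7.8% | 8.6% |
| 0.9 | 7.5% | 8.0% |

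A separate simulation with 75 per arm and one prognostic factor gave 8.8%, 8.7% and 8.3% at r = 0.3, 0.5 and 0.7. Three independent tests would give 1 − 0.95³ = 14.3%. That figure does not apply, because the three analyses share the same data.

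**The case against.** The strongest reply is that the efficient analysis is already planned and the paragraph is being over-read. The clause about determining the treatment effect may only describe how a change score works. The regressions that follow are planned with equal force, and the labels look like a conventional sequence of increasing adjustment. On that view nothing says the change score leads, and the lead model for a secondary outcome can be left to the analysis plan.

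Much of this stands. A reader might infer that the plan both loses precision and gives three chances at significance. The text does not support the two together. If the change score decides, there is one deciding test at about 5%. If nothing decides, model 1 is among the planned results and its precision is not lost. Nor is the change score invalid: after randomisation it is unbiased and holds its own error rate.

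What does not stand is that this is only detail left to another document. The article itself fixes the three methods and the significance rule, and it describes the change score alone as determining the effect. An analysis plan may settle the order, but this wording would then need to agree with it.

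Two further cautions are fair. Wound volume with many zeros is awkward for linear regression; the change score has the same difficulty. Wound volume and EQ-5D-5L are also measured at several visits, so naming model 1 without a time point would still not define one result.

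**Conclusion.** The point holds as a matter of priority among planned analyses. The plan lists a change score, model 1 and model 2 under one 5% rule and does not put the more efficient model 1 first.

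The size depends on the reading. Under the first, variance is 5% to 54% higher for r from 0.9 down to 0.3, assuming equal SDs. Under the second, the chance of a false positive is about 8% to 10% per outcome, and only if the best of the three is claimed. The values of r, k and g are assumptions.

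The point is limited to continuous secondary outcomes with a baseline value. The primary outcome, the sample size and the trial's main conclusion are unaffected.

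**What to change.** Reword the continuous-outcome sentences in Primary and secondary outcomes so that they state:

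1. For outcomes with a baseline value (EQ-5D-5L and wound volume), the treatment effect, confidence interval and P-value come from model 1: the follow-up value regressed on treatment and baseline, at one stated time point per outcome. The 26-week visit, where the primary outcome is assessed, is one candidate.
2. Model 2 and the change score are supportive. They are reported beside model 1 and not used to claim significance. The change score need not be deleted.
3. The change score and model 1 do not apply to outcomes with no baseline, such as ulcer-free days and costs. Those are analysed by a separately named method.

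The cost is a few sentences, and any analysis plan must agree with them. Model 1 is already planned. EQ-5D-5L is already collected at baseline, and a baseline wound volume is already implied by the planned change score. No visits, patients or software are added.

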### Follow up measurements

Patients will be followed up at predefined time points. This will coincide with routine outpatient visits ordinarily scheduled at 4, 10, 18, 26, 39 and 52 weeks from randomisation with phone consultations every fortnight to determine total ‘ulcer-free’ days following healing. At each scheduled visit, the wound will be assessed in terms of location (exact; forefoot vs. hind- and mid-foot), depth, dimensions, wound volume and wound area (as measured by Silhouette™ [Aranz Medical]), wound quality (patchy vs. confluent, % epithelialisation), probe to bone test and photography. Both feet will be assessed for new wounds. Blood tests will be (lipids, C-reactive protein, full blood examination and renal and liver function tests) will be performed as clinically indicated, but an HbA_1c_ will be measured at 3, 6 and 12 months to determine the change from recruitment. All patients will receive standard care related to off-loading, ongoing diabetes management and infection management as per the usual management protocol of the multi-disciplinary foot ulcer teams. In addition to baseline, an EQ-5D-5 L [22] will be performed at 26 and 52 week visits to ascertain change in health-related quality of life [24]. The primary outcome will be assessed at the 26-week visit.

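### The stated method for continuous secondary outcomes does not estimate the wound-healing trajectory, and it leaves the visit open

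*Protocol article*

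**What the plan says.** All references are to the protocol article.

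- **Secondary outcomes** lists, as item iii, the "trajectory of wound healing of the index ulcer", defined as volume and measured with a wound-imaging device.
- **Follow up measurements** has routine visits "scheduled at 4, 10, 18, 26, 39 and 52 weeks from randomisation". Volume and area are among the wound assessments made at every one of them.
- **Primary and secondary outcomes** (under Statistical considerations) gives one approach for continuous secondary outcomes: "change score analysis that determines treatment effect based on the difference between baseline and post treatment score (basic adjustment"). Two linear regressions follow: model 1 adjusts for the baseline value, and model 2 adds prognostic factors.
- The same section dates the binary outcomes: "Binary secondary outcomes at 12 months will be analysed similarly". Follow up measurements places the primary outcome at the 26-week visit. The rule for continuous outcomes has no date.

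The article mentions no repeated-measures model, slope, area under the curve or treatment-by-visit term.

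**The concern.** A trajectory is a course over time. A difference between baseline and one later value is not a course, whichever later value is used. Models 1 and 2 improve precision by adjusting for baseline, but they have no time term and no within-patient correlation, so they also take one later value per patient. The outcome as named and the method as stated do not match.

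Six visits could each supply the later value. If treatment speeds closure, the arms separate early and converge later as ulcers close in both. The same true effect can then look large or small according to the visit. If the visit is settled after results by arm are known, the 5% error rate for this outcome no longer holds.

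**Working it through.** **The plan's own figure.** The article gives no figure for outcome iii. Its sample size for the primary outcome reproduces. With p1 = 0.45, p2 = 0.70, d = 0.25, mean proportion 0.575, two-sided 5% and 80% power:

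n = [1.960·√(2·0.575·0.425) + 0.842·√(0.45·0.55 + 0.70·0.30)]² / 0.25² ≈ 60.2 per arm.

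Continuity correction: (n/4)·[1 + √(1 + 4/(n·d))]² ≈ 68 per arm, or 136 in total, as stated. Nothing below changes it.

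**Inputs for the illustration.** From the documents: 150 patients, taken as 75 per arm; 45% and 70% healed at 6 months (week 26); six visits; two-sided 5%. Assumed, because the documents give no values: lognormal baseline size with median 10 cm² and log SD 0.6; size (area) falling linearly to closure; lognormal healing time with log SD s of 0.6, 0.9 or 1.2; correlation 0.5 between baseline size and healing time; 15% measurement error.

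**Healing times.** If p is the proportion closed by week 26, the median is 26·exp(−s·z_p). For s = 0.9 this is 26·exp(0.9·0.126) ≈ 29 weeks in control and 26·exp(−0.9·0.524) ≈ 16 weeks in the treated arm.

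**Power by visit** (simulated; ranges are over s):

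| Analysis | Week 10 | Week 18 | Week 26 | Week 52 |
|---|---|---|---|---|
| Change score | 74-85% | – | 38-62% | 7-29% |
| Model 1 (baseline-adjusted) | 87-90% | 87-90% | 81-83% | 40-67% |

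The baseline-adjusted mean of weeks 4, 10, 18 and 26 has 90-91% power. Repeat runs agree with these figures to within about 3 points.

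**Gain over model 1 at one early visit.** For s = 0.6/0.9/1.2 the four-visit mean gives 90/91/91%. Model 1 gives 87/90/88% at week 10 (gain 3/1/3 points) and 90/89/87% at week 18 (gain 0/2/4 points). The gain is therefore 0-4 points.

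**Why the change score fades.** For a closed ulcer, the change is minus the baseline size in either arm. By the planning assumption (45% + 70%)/2 = 57.5% of ulcers are closed at week 26, so the change score increasingly carries baseline variation. Model 1 removes much of that, which is why it holds up better.

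**A second model with different assumptions.** Let the mean fraction of volume remaining be exp(−0.05t) in control and exp(−0.075t) in treated patients, with SD 0.4 and 75 per arm. The difference is 0.819 − 0.741 = 0.078 at week 4, 0.407 − 0.259 = 0.147 at week 18 and 0.074 − 0.020 = 0.054 at week 52. Power at the six visits is 22, 54, 62, 51, 27 and 13%. The levels differ, but the dependence on visit is the same.

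**False positives under free choice of visit.** For six independent tests, 1 − 0.95⁶ = 26.5%. Between-visit correlations of 0.5 to 0.9 bring this to about 23% down to 11%. In the wound-size simulation with no treatment effect, at least one of the six visits gives p < 0.05 in about 14-15% of trials.

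**The case against.** The strongest reply is that the sentence on continuous outcomes is generic. It never mentions the trajectory, and a score before and after treatment fits the quality-of-life instrument naturally. The section also gives no method for time to full epithelialisation, so it evidently does not cover every secondary outcome. An analysis plan that is not shown could name a visit or add a longitudinal model. This limits the point but does not remove it. The article states a method for continuous secondary outcomes without exempting this one, and that method does not fit an outcome named as a trajectory.

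Some stronger readings are tempting, but the documents do not support them:

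- *Five of six measurements are necessarily discarded, and patients who miss the chosen visit drop out.* The article does not limit the analysis to one visit, since the change score and both models could be run at each. It also gives no missing-data rule specific to continuous outcomes, so complete-case analysis would be an inference.
- *Late analyses carry almost no information.* The unadjusted change score is weak late on, but model 1 is also planned and has 81-83% power at week 26 in the illustration. The difference in proportions closed is itself treatment effect. Nothing in the article selects week 52.
- *A longitudinal model would add much power.* Against model 1 at week 10 or 18, it adds 0-4 points. In one variant closer to volume (baseline log SD 1.0, size shrinking as the 1.5 power of the linear fraction) it added nothing: 72% against 74% for week-10 model 1.
- *Hypothesis 1 rests on this outcome.* Time to full epithelialisation addresses healing time directly, with ulcer-free days and the primary outcome alongside. Outcome iii is supportive.

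**Conclusion.** The point holds in a limited form. The method stated for continuous secondary outcomes does not estimate the trajectory named as outcome iii, and the undated later value leaves the result open to the choice of visit. The dependence on visit is large in the illustration: 74-85% against 7-29% power for the change score, and 87-90% against 40-67% for model 1, at weeks 10 and 52. The false-positive chance under free choice is about 14-15%.

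These figures rest on assumed wound-size distributions, healing-time spread, correlation and measurement error, and on area as a stand-in for volume. The mismatch between outcome and method does not depend on them. Only a secondary outcome is affected. It is worth correcting because the data are already scheduled and only wording has to change.

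**What to change.** For outcome iii, replace the single-difference rule with a repeated-measures model that uses all scheduled visits to week 26, with weeks 39 and 52 as supportive. Include treatment, visit, treatment-by-visit and baseline volume.

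- Pre-state one contrast: the average baseline-adjusted treatment difference over weeks 4-26.
- Report the visit-specific differences with it as the course over time. The average alone is a mean level, not a trajectory.
- Because many volumes will be zero, use robust or bootstrap standard errors or a suitable transformation, and check model fit.
- The single-visit change can stay as a descriptive summary.

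Patients who miss a visit still contribute through their other visits. Fix the wording before any comparison by arm is seen; the Data Availability statement says that no data had yet been generated.

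The cost is a change of wording and a standard model, with no new measurements and no change in sample size. The drawbacks are that the summary is an average over visits and that model fit with many zeros needs attention.
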